#### **4.5 Discontinuation criteria**

##### **a) Individual subjects**

Reasons for the discontinuation of the treatment of single patients during or after the study are:

- withdrawal of Informed Consent;
- evident lack of compliance of the patient;
- onset of HIV during the trial period;
- pregnancy;
- not permitted co-medication if it is a safety risk for the patient;
- relevant protocol deviation if it is a safety risk for the patient;
- severe surgical complications during the transplantation if it is a safety risk for the patient;
- lost to follow-up;

Whenever possible, patients in whom the investigational treatment is discontinued prematurely will be followed up until the scheduled end of the period of observation. Unless a patient withdraws his/her informed consent, is lost to follow-up or continued study participation presents an intolerable risk, withdrawal from treatment does not lead to withdrawal from the scheduled examinations or from the trial.

**b) Entire trial**

The study can be terminated:

- In cases of not previously reported risk, accumulation of serious adverse drug reactions resp. adverse events, relevant protocol deviations. The decision is taken by the investigator and the respective manufacturer is informed.
- If there are major arguments against continuation, the principal investigator has the right to terminate the study prematurely.

**4.6 Drug responsibility****1. ATG-Fresenius S**

- a) Labelling of the investigational drug:  
The label of ATG-Fresenius S will be the commercial label of the product for Switzerland.
- b) Specification of the way of delivery and the record of the receipt of medicinal products:  
The investigational drug is usually delivered in a commercial manner to the investigator. The investigational drug is produced and stored in Gräfelfing. Following release by Quality Control the drugs are shipped directly to the pharmacy of the investigation center.
- c) Regulations concerning the storage in the clinic/practice:  
The investigational drug has to be stored protected from light and dry at a temperature of +2° C to +8° C. The investigator is directly responsible for the storage of the investigational drug.  
  
Only collaborators involved directly into this study have access to the investigation drugs. The dispersion and use of the investigational drugs has to be documented on separate form sheets (see enclosure 2).
- d) Regulation concerning the return of unused medicinal products at the end of the study or after expiry date, respectively:  
As ATG-Fresenius S will be bought in commercial manner, the investigator is responsible for the unused medicinal product. The use of ATG-Fresenius S has to be documented (see enclosure 2).

**2. Thymoglobulin**

- a) Labelling of the investigational drug:  
The labelling of Thymoglobulin will be the commercial label of the product for Switzerland.

- b)** Specification of the way of delivery and the record of the receipt of medicinal products:  
The investigational drug is usually delivered in a commercial manner to the investigator. Following release by Quality Control the drugs are shipped directly to the pharmacy of the investigation center.
- c)** Regulations concerning the storage in the clinic/pratic:  
Thymoglobulin is supplied in vials as a sterile, lyophilised powder to be reconstituted with sterile diluent. Vial 1 contains 25 mg freeze-dried rabbit anti-human thymocyte immunoglobulin. Vial 2 contains the diluent. Vials should be stored between the temperatures of +2° to +8°C (36° to 46°F); do not freeze the vials. Protect undiluted solution against direct light. Diluted medication is stable for 24 hours at 4°C or for 4 hours at room temperature.
- d)** Regulation concerning the return of unused medicinal products at the end of the study or after expiry date, respectively:  
As Thymoglobulin will be bought in commercial manner, the investigator is responsible for the unused medicinal product. The use of Thymoglobulin has to be documented (see enclosure 3).

## **5. SELECTION AND WITHDRAWAL OF SUBJECTS**

### **5.1 Study population**

Patient population: Consecutive recipients of a renal allograft who are at high immunological risk and who are at least 18 years or older. Two core centers will initiate the trial but other Swiss and foreign state centers are allowed to take part if they manifest their interest.

### **5.2 Inclusion criteria**

1. Recipients, who are at least 18 years or older and have a high immunological risk defined by:  
The presence of at least one donor-specific antibody (class I and/or II) detected and specified by flow-technology (FlowPRA and single antigen Flow-beads), which are
  - For class I below the threshold of detection of a current CDC T-cell-/ and B-cell cross-match
  - For class II below the threshold of detection of a current CDC B-cell cross-match.
2. Patient receives a renal allograft only.
3. Female patients of child bearing age agree to maintain effective birth control practice during the study.
4. Patient has been fully informed and has given written or independent person witnessed oral informed consent.

### **5.3 Exclusion criteria**

1. Patient is pregnant or breastfeeding.
2. Patient and donor are ABO incompatible.
3. Age of donor >75 years.
4. Patient has leukopenia, defined as having at transplantation less than 3.000/mm^3 leukocytes.
5. Patient has thrombocytopenia, defined as having at transplantation less than 75.000/mm^3 thrombocytes.
6. Patient is allergic or intolerant to ATG-Fresenius S, Thymoglobulin, steroids, Tacrolimus, MMF, or IVIG.
11. EBV risk constellation (recipient EBV negative and donor EBV positive).
12. Patient or donor is known to be HIV positive.
13. Patient has significant liver disease, defined as having during the past 28 days continuously ASAT (SGOT) and/or ALAT (SGPT) levels greater than 3fold of the upper value of the normal range of the investigational site.
14. Patient with malignancy or history of malignancy <2 years, except non metastatic basal or squamous cell carcinoma of the skin that has been treated successfully.
15. Patient has significant, uncontrolled concomitant infections and/or severe diarrhea, vomiting, or active peptic ulcer.
16. Patient is unlikely to comply with the visits schedule in the protocol.

## 6. TREATMENT OF SUBJECTS

### 6.1 Administration route, single dose, dosage, treatment period, follow-up for subjects

All patients included will provide written informed consent to participate in the trial.

Blood parameters will be determined before study drug administration which will be used as baseline values.

In women of childbearing age a pregnancy test will be performed before inclusion.

Patients qualified for the trial will be randomised to one or the other treatment.

The treatments will be administered as open therapies. A central venous catheter will be placed and kept open using a normal saline or glucose infusion drip or a fistula. This line will be used to administer test treatments.

Intravenous methylprednisolone sodium succinate (see table "therapy scheme I and II") should be given 1 hour before administering the test drugs.

Patients randomised to receive a bolus therapy with ATG-Fresenius S will be treated i.v. with a 9 mg/kg bw bolus of ATG-Fresenius S, which is diluted in 100-500 ml physiological saline. The infusion has to be applied completely before reperfusion (infusion time at least 1 hour). After this first infusion the patients receive 3 mg/kg bw/d for 4 days given over 4 hours.

Patients randomized to receive Thymoglobulin will be treated i.v. with 1.5 mg/kg bw of Thymoglobulin, which is diluted in 100-500 ml physiological saline. The infusion has to be completed before reperfusion (infusion time at least 1 hour). After this first infusion the patients receive 1.5 mg/kg bw/d for 3 days given over 4 hours.

The patients will be observed closely for the first 2 hours of treatment.

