#### 4.3.1 Primary endpoints

The main target variables are safety parameters. Variables to be assessed are incidences of selected adverse events. The primary outcome measure of the trial is the incidence of the following signs and symptoms (individually and in combination) at any time during randomized treatment and follow-up:

1. Anaphylaxis
2. Serum sickness
3. Two of the following symptoms: Fever  $>38^{\circ}$ , chills, nausea/vomiting or erythema
4. One of the following findings:
  - Hematological side effects (leucopenia ( $<3000$ ), thrombocytopenia ( $<50'000$ ), hyporegenerative anemia (hemoglobin  $< 100\text{g/l}$  plus non-elevated reticulocytes or erythropoietin substitution)
  - Severe infectious complications defined by prolonged hospital stay, needing ICU or re-hospitalization.
  - Lymphoma, post-transplant lymphoproliferative disease (PTLD), malignancy
  - Number of patients withdrawn due to adverse events or for other safety-related reasons

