## 6.6 Handling of the investigational drug

- a) Rules for the use of concomitant treatment:  
Sodium Heparin must not be added to the ATG-Fresenius S infusion solution or administered via the same route, because a pH below 5.2 may lead to turbidity.
- b) Measures to be implemented to ensure the safe handling of the drugs, measures to control close adherence to the instructions:  
ATG-Fresenius S is a hypotonic concentrate for infusion with pH 3.7. Before intravenous infusion it must be diluted with physiological saline solution.  
ATG-Fresenius S must only be administered according to the instructions of a physician and under medical supervision. Particular attention must be paid to monitoring the patient for any symptoms of anaphylactic shock. Close monitoring of the patient must continue for at least 30 minutes following the end of the infusion.  
For peripheral administration a large vessel should be chosen. It has been found that systemic tolerance is improved, if hydrocorticosteroids and/or antihistaminic drugs are administered prior to infusion.

- c) Thymoglobulin  
The powder should be mixed with the solvent that is added in the package. Thymoglobulin is infused after dilution in saline (0.9%) or dextrose (5%) solution (per one vial use 50 ml of infusion solution). Mix the solution by inverting the bag gently once or twice.  
Infuse slowly into a high-flow vein. Adjust the infusion rate so that the total duration of infusion is at least one hour for the first dose and over at least 4 hours for subsequent doses.

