## **7. ASSESSMENT OF SAFETY**

### **7.1 Specification of safety parameters**

All adverse events reported will be included in the safety evaluations with particular attention to the list mentioned in chapter 4.3.1. All symptoms will be inquired actively.

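### For the later 4-hour infusions the written minimum of close observation is longer for ATG-Fresenius S than for Thymoglobulin, so transient infusion reactions may be detected unequally

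*Protocol*

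**What the plan says.** Section 6.1 describes the infusions in both arms and then gives one observation rule for all patients: "The patients will be observed closely for the first 2 hours of treatment". The first infusion takes at least 1 hour in either arm. For the later days the section says, for ATG-Fresenius S, "After this first infusion the patients receive 3 mg/kg bw/d for 4 days given over 4 hours", and for Thymoglobulin, "After this first infusion the patients receive 1.5 mg/kg bw/d for 3 days given over 4 hours".

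Section 6.6 b), which concerns the handling of ATG-Fresenius S, adds: "Close monitoring of the patient must continue for at least 30 minutes following the end of the infusion". Section 6.6 c), on Thymoglobulin, gives dilution, vein and rate, with an infusion time of "at least one hour for the first dose and over at least 4 hours for subsequent doses". Neither it nor the Instructions for Administration that follow set a monitoring period.

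Section 4.3.1 makes anaphylaxis (item 1) and any two of fever, chills, nausea/vomiting or erythema (item 3) parts of the primary endpoint, counted "at any time during randomized treatment and follow-up". Section 7.1 adds: "All symptoms will be inquired actively". Section 9 plans a separate analysis of each listed reaction.

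**The concern.** Items 1 and 3 consist largely of signs that can come and go within an infusion or soon after it: a fall in blood pressure, stridor, flush, a short fever. Whether they are recorded depends partly on whether someone is watching. Treatment is open, and the stated minimum of close watching is longer in one arm for every infusion after the first.

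The blinded causality rating in Section 7.3 g) does not correct this. It classifies events that have been recorded and cannot recover one that was not seen. Because Section 9 analyses each listed reaction separately, the other parts of the composite would not absorb a detection difference in items 1 and 3. Item 3 needs two symptoms, so missing one of them can lose the event.

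Any such bias would add detected events to the ATG-Fresenius S arm. Section 3 assumes that the safety of ATG-Fresenius S may be superior, so the bias would work against that assumption. Section 2.2.4 also describes an earlier randomised comparison with somewhat more fever, and slightly higher scores for blood-pressure decrease and respiratory symptoms, under Thymoglobulin. That is the arm without the added rule.

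**Working it through.** The plan states no figure for total observation time, so there is nothing to reproduce. The check is what the text requires per infusion.

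**Inputs**
- Common rule (6.1): 2 h of close observation.
- Added rule, ATG-Fresenius S only (6.6 b): from the infusion to at least 0.5 h after its end. I read the word continue as implying close monitoring throughout the infusion.
- First infusion: at least 1 h in both arms (6.1).
- Later infusions: four of 4 h for ATG-Fresenius S, three of 4 h for Thymoglobulin (6.1).

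**Formula for an infusion of T hours**
- ATG-Fresenius S: max(2, T + 0.5).
- Thymoglobulin: 2 if the 6.1 rule applies to each infusion; nothing specified after the first if it applies only to the start of treatment.

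**Results**

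| Infusion | ATG-Fresenius S | Thymoglobulin |
|---|---|---|
| First, T = 1 h | max(2, 1.5) = 2 h | 2 h |
| First, T = 1.5 h | max(2, 2) = 2 h | 2 h |
| First, T = 2 h | max(2, 2.5) = 2.5 h | 2 h |
| Each later one, T = 4 h | max(2, 4.5) = 4.5 h | 2 h, or none specified |

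The first-infusion windows are equal up to T = 1.5 h. The gap lies in the later infusions: 4.5 − 2 = 2.5 h each, or 4.5 h on the narrower reading of 6.1.

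**Course totals with a 1-hour first infusion**
- ATG-Fresenius S: 2 + 4 × 4.5 = 20 h.
- Thymoglobulin: 2 + 3 × 2 = 8 h, or 2 h on the narrower reading.

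Of the 12 h difference between 20 and 8, 4.5 h comes from the fifth ATG-Fresenius S infusion, which is part of the design. The other 3 × 2.5 = 7.5 h comes from the observation wording. The per-infusion comparison is therefore the cleaner one.

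**What a detection loss would do (illustration; the assumptions are not in the documents)**
Take equal true rates p in both arms, 20 patients per arm (Section 9), and a share m of Thymoglobulin events missed. The apparent risk ratio, ATG-Fresenius S over Thymoglobulin, is 1/(1 − m), and the apparent risk difference is p × m.
- m = 10%: ratio 1/0.9 = 1.11. m = 30%: ratio 1/0.7 = 1.43.
- Risk difference: 0.2 × 0.1 = 0.02 at the low end and 0.6 × 0.3 = 0.18 at the high end.
- Chance of a two-sided Fisher p ≤ 0.15 (one of the working indicators in Section 9), by exact enumeration for p = 20%, 40% and 60%: 0.065 to 0.076 with no loss, and 0.067 to 0.275 with m from 10% to 30%.

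Only events arising in the time not covered for Thymoglobulin can be lost in this way. So m is the share of events falling in that time multiplied by the chance that such an event goes unrecorded. The documents give neither factor.

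**The case against.** Four counter-arguments carry weight.

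*The two rules do not exclude each other.* A reader might infer that 6.1 and 6.6 b) contradict each other for ATG-Fresenius S, or that the 2-hour rule is a Thymoglobulin rule. Neither reading is supported. The 2-hour sentence covers both arms, 6.6 b) sets a longer minimum for one product, and a site can meet both. The asymmetry comes only from the added sentence.

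*Handling text is not the ascertainment rule.* The endpoint window spans all of treatment and follow-up. Symptoms are actively inquired about (7.1), adverse events are documented continuously (7.2), and both products are given under medical supervision (6.5), all without distinction by arm. A reader might infer that Thymoglobulin patients go unobserved for part of the infusion, or that the endpoint is in fact ascertained unequally. The documents do not say so; they only stop specifying close observation. This stands, and it limits the point to a risk. It does not remove the risk, because asking about symptoms is weaker than watching for brief signs, and the scheduled vital signs in Section 6.2 are daily.

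*Reactions are expected mainly at the first dose.* Section 2.5.1 says that ATG-Fresenius S reactions usually appear only then, and Section 2.5.3 speaks of first-dose effects for Thymoglobulin. At that dose a 1-hour infusion gives equal windows. This stands and narrows the effect. However, Section 2.5.1 also places the risk at any time during an infusion or shortly after it.

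*Most of the composite is untouched.* Serum sickness, cytopenias, severe infections and malignancy do not depend on bedside observation during an infusion. This also stands; the exposure is in items 1 and 3.

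**Conclusion.** The wording asymmetry is real. For each infusion after the first, the text requires at least 4.5 h of close observation for ATG-Fresenius S and 2 h for Thymoglobulin, or no stated period if the 2-hour rule covers only the start of treatment. At a 1-hour first infusion there is no difference. This rests on 4-hour later infusions and on reading 6.6 b) as covering the whole infusion.

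The consequence is a possible detection bias against ATG-Fresenius S in items 1 and 3, limited to transient reactions during or shortly after the later infusions. The documents do not show that such a bias occurs and give no basis for its size. The risk ratios and probabilities in the illustration follow from assumed loss rates and are not estimates. The point justifies harmonising the text. It does not support a claim that the primary endpoint is compromised.

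**What to change.** Reconcile Sections 6.1 and 6.6 so that observation for infusion reactions is described in the same way for both arms. The text should state which infusions it covers and from which reference point (start or end of infusion) it is measured. How long the observation lasts and what it consists of are clinical matters for the sponsor; no view on them is offered here.

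The change is a short edit to the protocol text. It may mean slightly more bedside recording in one arm. Sample size and planned analyses are unaffected, and the difference of five against four infusions remains by design.

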### 6.2 Transplant monitoring

#### Standard monitoring:

- The patients will be followed by the routine clinical, biochemical and imaging parameters.
- Blood pressure, heart rate, temperature and urine output will be recorded daily during hospitalisation.
- Standard blood work as routinely done includes:
  - Complete blood count (including hemogram, leukocytes, reticulocytes and platelet count).
  - Complete blood chemistry (including serum creatinine, blood urea nitrogen (BUN), sodium, potassium, calcium, phosphate, uric acid, total protein, albumin, bilirubin, SGOT (AST), SGPT (ALT), LDH, gamma-GT, alkaline phosphatase, glucose, cholesterol and HbA1c).
- Standard blood work will be performed at each visit and at least at days 0, 1, 7, 14 and at months 1, 3, 6, 12 and 24.

**Optional monitoring:**

- Protocol allograft biopsies will be done on day 7 post-transplant, at month 3, 6, and 12.
- Lymphocyte subpopulations consisting of cells positive for CD3, CD4, CD8, CD19, and CD56 will be measured by flow-cytometry before transplantation, daily for the first 7 days, at month 1, 3, 6, 12, and 24.
- Monitoring for viral infection/reactivation (e.g. Decoy cells in urine, Polyoma-BK-viremia, EBV-viremia, CMV-antigenemia or CMV-viremia).

**6.3. Diagnosis and treatment of rejection episodes**

Clinical acute rejection episodes are defined by an increase of serum creatinine of >20% from baseline with consisting histology classified according to local practice.

Subclinical acute rejection episodes are defined by a protocol biopsy with consisting histology classified according to local practice.

The treatment of rejections is ad libidum of the physician, however, a cross-over treatment as rescue-therapy by using the immunoglobulin preparation (AFG-Fresenius S or Thymoglobulin) from the other group is prohibited.

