**Two immunosuppressive protocols will be compared:**

1. a regimen consisting of a triple drug therapy with Tacrolimus, MMF, and steroids as basis therapy plus IVIG for 5 days (total dose 2g/kg bw, max. 140g). In addition, the patients receive intra-operative 9 mg/kg bw ATG-Fresenius S (completed before reperfusion), followed by 3 mg/kg bw/d for the next 4 consecutive days.

vs.

2. a regimen consisting of a triple drug therapy with Tacrolimus, MMF, and steroids as basis therapy plus IVIG for 5 days (total dose 2g/kg bw, max. 140g). In addition, the patients receive intra-operative 1.5 mg/kg bw Thymoglobulin (completed before reperfusion), followed by 1.5 mg/kg bw/d for the next 3 consecutive days.

After kidney transplantation in end stage renal disease patients it is assumed that:

- the safety profile of ATG-Fresenius S may be superior to that of Thymoglobulin
- the efficacy profile of both treatments is clinically equivalent

The aim is to obtain preliminary information on the safety and efficacy of two induction treatment protocols – ATG-Fresenius S and Thymoglobulin – in immunological high risk patients under basal immunosuppression with Tacrolimus, MMF and steroids used in the prevention of acute rejection following renal transplantation.

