#### **4.3.2 Secondary endpoints**

- Incidence of acute rejection episodes and type (cellular or humoral) of rejection (according to Banff)
  - Total number and type of anti-rejection treatments
- Graft function
  - Serum creatinine at day 1, 7, 14, and month 1, 3, 6, 12
  - Proteinuria month 1, 3, 6 and 12
- Graft and patient survival

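### Section 6.3 does not say which creatinine is the reference for clinical rejection, and the only baseline the protocol defines would exclude most for-cause, biopsy-proven rejections in a working graft

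*Protocol*

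**What the plan says.** - **Creatinine rule.** Under Section 6.3, clinical acute rejection is "defined by an increase of serum creatinine of >20% from baseline with consisting histology classified according to local practice". Subclinical rejection, in the same section, needs a protocol biopsy with matching histology and has no creatinine criterion. Section 6.3 does not define its baseline.
- **Baseline.** Section 6.1 gives the only definition for blood values: "Blood parameters will be determined before study drug administration which will be used as baseline values". On the first dose of ATG-Fresenius S it adds "The infusion has to be applied completely before reperfusion (infusion time at least 1 hour", and it sets the same timing for Thymoglobulin. Section 6.2 includes serum creatinine in the standard blood work.
- **Population.** Section 3 describes the recipients as having end-stage renal disease: "After kidney transplantation in end stage renal disease patients it is assumed that".
- **Classification.** Section 4.3.2 lists the endpoint as "Incidence of acute rejection episodes and type (cellular or humoral) of rejection (according to Banff". Section 6.3 leaves histology to local practice for both clinical and subclinical episodes.
- **Protocol biopsies.** The list in Section 6.2 that is headed as optional monitoring contains "Protocol allograft biopsies will be done on day 7 post-transplant, at month 3, 6, and 12". The tacrolimus target table in Section 6.4 makes its steps at months 3, 6 and 12 depend on a normal protocol biopsy.
- **Use of the endpoint.** Section 9 analyses rejection incidence, time to first and second rejection, number per patient, duration and reversal. Section 3 speaks of clinical equivalence up to ±15 percentage points in rejection rates.

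**The concern.** A case definition has to tell both centres which creatinine value to compare against. Section 6.3 does not. The only baseline available in the protocol is the value of a patient with end-stage renal disease before the graft has been perfused. A working graft brings creatinine well below that value. A rise that signals rejection in such a graft would usually still lie below the pre-transplant value, so it could not exceed it by 20%.

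Two further inconsistencies bear on the same endpoint. One concerns the histological classification, the other whether every patient has protocol biopsies. The second matters because subclinical rejection can be found only on those biopsies, so its count depends on who is biopsied. At stake are the rejection rates and every rejection summary in Section 9.

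**Working it through.** The protocol derives no figure from this definition, and its 40 patients are set by feasibility, so there is no stated number to reproduce. The check compares thresholds.

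**Inputs**
- Functioning-graft creatinine: 158 µmol/l, the average in a cited ATG-Fresenius S series (Section 2.2.4). It is the only such figure in the protocol.
- Pre-transplant creatinine: not given. Assumed range 400 to 1000 µmol/l.

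**Thresholds**
- Graft-referenced: 1.2 × 158 = 190 µmol/l.
- Literal, with the Section 6.1 baseline: 1.2 × 400 = 480 µmol/l up to 1.2 × 1000 = 1200 µmol/l.
- Ratio of literal threshold to graft value: 480/158 = 3.0 up to 1200/158 = 7.6. That is a rise of about 204% to 659% instead of 20%.
- With graft values of 120 to 200 µmol/l (assumed), the multiple runs from 480/200 = 2.4 to 1200/120 = 10.
- A doubling from 158 to 316 µmol/l would qualify only if the pre-transplant value were below 316/1.2 = 263 µmol/l, which is outside the assumed range.

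**How episodes are classified under the literal reading**

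| Episode with confirming histology | Clinical? | Subclinical? |
|---|---|---|
| Functioning graft, for-cause biopsy, creatinine below the literal threshold | No | No, not a protocol biopsy |
| Found on a protocol biopsy | Only if the threshold is exceeded | Yes, no creatinine rule |
| Graft that never worked or failed severely, for-cause biopsy | Possibly | No |

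The gap is the first row. An episode there would count as no rejection, yet its treatment would count under the anti-rejection treatments in Section 4.3.2.

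**If the literal reading is not applied.** Section 6.3 then has no reference at all. One centre might use the lowest post-transplant value and the other the last stable value. With 20 patients planned at each centre (Section 9), rejection would be counted under two rules, with no known direction of error.

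**Classification and biopsies side by side.** Section 4.3.2 says Banff and Section 6.3 says local practice, for the same endpoint. Section 6.2 places protocol biopsies under an optional heading but states that they will be done, and Section 6.4 presupposes their result.

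**The case against.** The strongest reply is that Section 6.3 does not refer back to 6.1, whose baseline sentence is a general one about blood parameters. Transplant physicians would hardly apply a rule that a functioning graft could almost never meet. That stands as a limit: the documents do not show that sites will use the pre-transplant value. It does not rescue the definition, because without 6.1 the reference is missing.

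On classification, Section 8 sends efficacy assessment to 4.3.2, so the endpoint does have a named system, and 6.3 may be read as describing local diagnosis. That softens the contradiction but does not remove it, since 6.3 is where the episodes are defined.

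A reader might infer three stronger things, none of which the documents support:

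- **That confirmed rejections generally go uncounted.** Those found on a protocol biopsy count as subclinical whatever the creatinine, and a graft that never worked could exceed even the literal threshold.
- **That the definition pulls the arms together and favours equivalence.** If half of all rejections were missed equally in both arms, an illustrative 30% versus 50% would become 15% versus 25%, a gap of 10 points instead of 20. That needs the literal reading and equal loss in each arm. Nor is the ±15-point statement tied to any test in Section 9. With 20 per arm, the 95% half-width 1.96 × √(2p(1−p)/20) is about 21 points at p = 0.13 and 31 at p = 0.58, so an interval inside ±15 points is out of reach at such rates under any definition.
- **That biopsies will be selective by arm.** The protocol also says that they will be done, and only the open design points towards selection.

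**Conclusion.** The point holds as a defect of definition. Section 6.3 gives no creatinine reference, and the one baseline the protocol offers would set the threshold at about 3.0 to 7.6 times the cited graft value. Under that reading, most for-cause, biopsy-proven rejections in a functioning graft fall into neither category. Under any other reading, the rule is left to each centre. The size rests on the assumed pre-transplant range of 400 to 1000 µmol/l and on a single graft average from a cited series. The missing reference and the two inconsistencies rest on the text alone.

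Rejection is one of several secondary endpoints in a descriptive pilot, and the primary safety analysis does not use it. This should be fixed, but it does not put the primary result in doubt. A later analysis plan could settle the creatinine reference. It could not restore uniform histology or biopsies that were never taken.

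**What to change.** For endpoint counting only, and leaving treatment decisions as they are:

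1. State in Section 6.3 a post-transplant creatinine reference, for example the lowest value before the episode. In grafts with delayed function, count rejection proven on a for-cause biopsy on histology alone.
2. Replace local practice with Banff in 6.3, to match 4.3.2.
3. Keep all acute rejection as the endpoint in 4.3.2, but report clinical and subclinical rejection separately. Use the patients actually biopsied at each time point as the denominator for subclinical rejection. Say that an episode meeting both definitions is counted once in the total.
4. Reconcile Sections 6.2 and 6.4 on whether protocol biopsies are optional. No view is taken here on which clinical rule is right.

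The cost is protocol wording and one extra denominator per biopsy time point. Creatinine is already measured serially, Banff is already named for the endpoint, and items 1 to 3 need no additional biopsies.
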